### Recruitment

Daily visit to the stroke inpatient ward is planned at Acharya Vinoba Bhave Rural Hospital, and if the patient is willing to enroll in the said study can be recruited for the study after written informed consent. Patients will be added one at a time until the target sample size is reached.

### Setting

Locus of the study: out patient department and inpatient department of Panchakarma & Kayachikitsa department, Mahatma Gandhi Ayurveda College Hospital and Research Centre (MGACH&RC), Salod (Hirapur) Wardha, Maharashtra. & Department of Neuro physiotherapy, Ravi Nair Physiotherapy College, Sawangi, Wardha Maharashtra, Datta Meghe Institute of Higher Education and Research, Wardha, Maharashtra.

Study setting: The study will be conducted in
*Panchakarma* OPD & IPD, Mahatma Gandhi Ayurveda College Hospital and Research Centre (MGACH&RC), Salod (Hirapur) Wardha, Maharashtra.

Patients will be recruited after approval from Clinical Trials Registry - India (CTRI), and the exposure period for treatment will be one month. The follow-up will be conducted on the 60
^th^ and 90
^th^ day of treatment.

Criteria for discontinuing or modifying: if patients are willing to quit in between they will be allowed to quit and will be replaced; if the patient develops an acute illness during the trial, which may hamper the study and withdrawn patients will be replaced.

### Participants

Diagnosed stroke cases will be enrolled in the study with the computerized randomization method.

### Eligibility criteria

The inclusion criteria for the study are the patients with the first stroke diagnosed with CT/MRI (thrombolytic stroke only) without other neurological deficits but < six months of onset, patients diagnosed as stroke with ICD code 2020 ICD-10-CM Diagnosis Code I69.351 patients between 45 to 60 years of age irrespective of gender/occupation and socio-economic status. Patients with controlled hypertension and Non-insulin dependent Diabetes Mellitus (NIDDM). Patient with ankle dorsiflexion stage 1 to 2 and ankle plantar flexors spasticity 1+ on. Patients are willing to give informed consent and ready to follow simple instructions.

The exclusion criteria for the study are the patients having a thrombolytic stroke with onset for > six months, subjects with complications such as uncontrolled metabolic disorders and severe systemic disorders, e.g., renal or cardiac failure, altered sensorium, or coma. Those who are on tube feeding or intravenous fluid therapy. The patients of stroke with a history of trauma (
*Abhighatajanya*), onset due to intracranial space-occupying lesions, post-surgical or postpartum complication, degenerative disorders of the brain or intracranial infectious disease or hemorrhagic nature. The patients with specific medical and psychological contraindications for electrical stimulation Brooks,
^
4
^ patients with visual or auditory difficulties, anti-anxiolytic treatments. Pregnant women and lactating mothers will also be excluded. Patients contraindicated for
*Basti & Swedana* therapy and patients with fixed ankle or foot contracture, pacemakers, and a metal plate in the lower limb will be excluded.

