### Assignment of interventions (for controlled trials)

Patients will be recruited by simple randomization through the computer-generated table. The principal investigator (PI) and co-investigator (CO-I) will allocate and enroll the patient. Using computer-generated random numbers, the researcher creates random allocation cards. The researchers will keep the original randomly assigned sequences in a safe place and use a different copy to sign up the patients.

The envelopes will be marked with serial numbers on the outside. The date, time, patient ID, post-procedure results, and other required details will be on the envelope.

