### Data collection, management, and analysis methods

For retention of patients, appointment reminders will be scheduled, and question-answering sessions will be planned. The complete follow-up will be mentioned in the patient file, and if patients are required to withdraw or discontinue, the patient file will be closed and maintained for the record purposes.

Observations will be made after the completion of the study, according to the data collected with the help of the following:
I.Case registration form with detailed history and examinationsII.Follow-up assessment proforma

The principal investigator and co-investigator will do data monitoring and coding. Data entry will be done in soft copy and case record form in hard copy. The values will be verified twice before submission in soft copy. Each file of the patient is secured with a specific patient code.

The data obtained will be calculated using the Student’s Paired ‘t’-test and Unpaired ‘t’ test for objective variables with
SPSS statistical software.

*To verify the significance of the results*

Improvements in Fugl-Meyer assessment-35%, one leg stance test-20%, functional reach test-35%, quality of life scale-25%, Barthel index-25% and NIH stroke-scale-score-20% will be considered as significant.

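### Time since stroke onset may be anything below six months, yet neither allocation nor the unpaired t-test uses it: precision is lost, though the randomised comparison is not biased

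*Protocol article*

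**What the plan says.** All references are to the protocol article.

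- **Eligibility criteria.** Entry is for first strokes "without other neurological deficits but < six months of onset". The matching exclusion is "thrombolytic stroke with onset for > six months". Participant timeline repeats the upper limit. No section gives a lower limit.
- **Assignment of interventions.** "Patients will be recruited by simple randomization through the computer-generated table". No strata are named.
- **Data collection, management, and analysis methods.** "The data obtained will be calculated using the Student’s Paired ‘t’-test and Unpaired ‘t’ test for objective variables". No covariate is named. The same section lists percentage improvements (for example 35% on Fugl-Meyer and 20% on NIHSS) that will count as significant, and does not say that they are differences from control.
- **Sample size.** 20 per group, chosen on practical grounds.
- **Recruitment and Setting.** Recruitment says "Daily visit to the stroke inpatient ward is planned at Acharya Vinoba Bhave Rural Hospital". Setting names the "out patient department and inpatient department of Panchakarma & Kayachikitsa department" of a different hospital.

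Time since onset therefore serves only as an entry criterion.

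**The concern.** The outcomes are recovery measures read at days 30, 60 and 90, and the question is how much recovery Basti adds. A patient enrolled soon after the stroke and one enrolled months later may expect different recovery over the same 30 to 90 days on standard care alone. The article itself treats time since onset as important enough to be both an inclusion and an exclusion criterion.

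If the variable is prognostic, leaving it out of the comparison has two costs. Its spread stays in the error term and lowers power. And in the one trial that will be run, the arms may differ in it by chance with nothing in the analysis to correct for that. The onset date has to be known to check eligibility, so the information is there and goes unused.

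**Working it through.** The article gives no alpha, power, effect size or SD, so 20 per group cannot be reproduced. The check asks what ignoring time since onset costs at that size.

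**Inputs.** From the article: 20 per arm, onset from 0 to under 6 months, simple randomisation, paired and unpaired t-tests. Assumed, because the article gives no figures: onset uniform over 0 to 6 months; time since onset explains a share R² of 10%, 25% or 50% of the variance of change; treatment effect 0.8 SD of change; two-sided 5% level.

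**1. Chance imbalance.** SD of onset = 6/√12 = 1.73 months. Standard error of the difference in arm means = 1.73 × √(2/20) = 0.55 months.

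- P(difference > 0.5 month) = 2 × [1 − Φ(0.5/0.548)] = 36%
- P(difference > 1 month) = 2 × [1 − Φ(1/0.548)] = 6.8%
- P(difference > 1.5 months) = 0.6%

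Half of these imbalances favour control, so an imbalance above one month in favour of Basti arises in about 3.4% of trials.

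**2. Type I error.** In 20,000 simulated trials per setting with no treatment effect, the unpaired t-test rejected in 4.9 to 5.4%. ANCOVA on onset rejected in 4.6 to 5.7% (4,000 trials per setting). Both agree with 5%.

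**3. The minority of trials with an imbalance above one month.**

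| R² | Rejection by the unadjusted t-test, no true effect | Mean spurious difference when the imbalance favours Basti |
|---|---|---|
| 10% | 9 to 10% | about 0.22 SD |
| 25% | 16 to 18% | about 0.35 SD |
| 50% | 30 to 31% | about 0.49 SD |

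**4. Precision.** Power ≈ Φ(0.8 / [√(1 − R²) × √(2/20)] − 1.96). The n per arm for 80% power is 2 × (1.96 + 0.84)² × (1 − R²)/0.8², rounded up.

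| R² | Power at 20 per arm | n per arm for 80% power |
|---|---|---|
| Unadjusted | Φ(2.53 − 1.96) = 72% | 25 |
| 10% | Φ(2.67 − 1.96) = 76% | 23 |
| 25% | Φ(2.92 − 1.96) = 83% | 19 |
| 50% | Φ(3.58 − 1.96) = 95% | 13 |

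These are normal approximations for onset alone. They ignore the small loss of degrees of freedom and any further gain from the baseline score.

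**5. Within-group tests.** With natural recovery only, and a mean change of 0.5 or 1.0 SD (assumed), the paired t-test in group B is significant in about 57% or 99% of trials.

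**The case against.** A reader might infer that natural recovery can pass for a treatment effect in the comparison of the arms. The documents do not support that. Group A is a concurrent randomised control on the same standard treatment and physiotherapy, recovery occurs in both arms, and its spread is already in the t-test's standard error. Step 2 shows no inflation. Step 3 describes selected trials, whose excess rejections are offset in the better-balanced ones. This objection stands in full. Recovery passes directly for effect only through the within-group paired tests and the percentage thresholds.

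A reader might also infer that two recruitment sources are declared. Only Recruitment names a source. Setting says where the study is conducted, and recruiting at one hospital while treating at another fits both sections. What remains is an unreconciled description that leaves the mix of early and later patients undefined.

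The size of the gain is also open to challenge. Recruitment from the ward alone, and the exclusion of patients with altered sensorium, tube feeding or intravenous fluids, may narrow the spread of onset. An illustrative curve points to modest R². It assumes 10 recoverable points, exponential recovery with a time constant of 30 to 60 days, and onset uniform over 7 to 180 days. The between-patient SD of natural gain is then about 0.9 to 1.2 points at day 30. If other variation has SD 3 to 6 points (also assumed), R² runs from 0.9²/(0.9² + 6²) = 2% to 1.2²/(1.2² + 3²) = 14%. The same steps at day 90 give 8 to 29%. On that reckoning 50% is optimistic, and the gain at day 30 may be small.

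Last, covariates are often left to an analysis plan, which is not shown here. But the article does not stay silent: it names the tests, and a t-test carries no covariate. If a fuller plan already specifies adjustment, the article should be brought into line with it.

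**Conclusion.** The point holds as one of efficiency and robustness, not of bias. The unadjusted between-arm t-test is valid: its type I error is about 5%, provided that allocation follows the random sequence. (The statement that "The principal investigator (PI) and co-investigator (CO-I) will allocate and enroll the patient" raises concealment, which is a separate matter.)

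The avoidable cost is a power of 72% against about 76 to 83% if onset explains 10 to 25% of the variance, and 95% in the optimistic case of 50%. About 7% of trials would have arm means more than one month apart. All these figures rest on the assumed uniform onset, R² and 0.8 SD effect; a narrower onset distribution would shrink them. The change is still worth making, because it uses values already collected and costs almost nothing if onset turns out to be weakly prognostic.

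**What to change.** 1. In Data collection, management, and analysis methods, replace the unpaired t-test as the between-arm analysis at days 30, 60 and 90 with ANCOVA. Adjust for the baseline score of the outcome and for days from onset to randomisation, with the form fixed in advance (for example log days). Cost: two degrees of freedom (40 − 2 = 38 become 40 − 4 = 36). No new data are needed, and eligibility and sample size do not change.
2. State that conclusions about Basti rest on this between-arm comparison. Keep the paired t-tests and percentage thresholds as description only. Cost: one sentence.
3. Reconcile Recruitment with Setting: say where patients are identified and where they are treated, so that the expected range of time since onset is clear. Cost: a clarification of wording.

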*Dashmoola Basti* with standard control over static and dynamic balance in stroke patients using the Single Limb Stance Test and Functional Reach Test, respectively. The secondary goal is to evaluate and compare the adjuvant role of
*Dashmoola Basti* with standard control over gait parameters (distance and time parameters), the Barthel Index, resistance experienced during passive range of motion based on the modified Ashworth scale, and the National Institute of Health (NIH) stroke-scale-score in stroke patients.

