### Variables to be measured

Improvements in the following assessment variables are expected as primary outcomes: Fugl-Meyer assessment for sensory-motor function of lower extremities, one-leg stance test, functional reach test for static and dynamic balance in patients, quality of life scale and Barthel index independent living of patients with Stroke, resistance experienced during passive range of motion based measured on Modified Ashworth scale NIHSS for improvements in clinical features of stroke are expected to be measured.
^
7
^

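### The Modified Ashworth scale is primary in one section and secondary in another, and the only named tests are t-tests, whose result on this ordinal scale depends on an unstated numeric code for grade 1+

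*Protocol article*

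**What the plan says.** Four places in the protocol article bear on this.

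- **Eligibility criteria.** Patients are admitted with "Patient with ankle dorsiflexion stage 1 to 2 and ankle plantar flexors spasticity 1+ on". The sentence stops there. It names no scale and does not say whether 1+ is the exact grade or a minimum.
- **Variables to be measured.** Under the lead-in "Improvements in the following assessment variables are expected as primary outcomes", the list includes "resistance experienced during passive range of motion based measured on Modified Ashworth scale". No muscle group is named.
- **Introduction.** After the opening "The secondary goal is to evaluate and compare the adjuvant role of", the list of secondary measures includes "resistance experienced during passive range of motion based on the modified Ashworth scale". The Abstract puts the scale among the main goals together with almost every other measure, so it does not settle the matter.
- **Data collection, management, and analysis methods.** The whole statistical method is "The data obtained will be calculated using the Student’s Paired ‘t’-test and Unpaired ‘t’ test for objective variables with" SPSS. No ordinal or rank method is named. The improvement criteria that follow are "Improvements in Fugl-Meyer assessment-35%, one leg stance test-20%, functional reach test-35%, quality of life scale-25%, Barthel index-25% and NIH stroke-scale-score-20% will be considered as significant". The Modified Ashworth scale is not among the six instruments.

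**The concern.** The rank of this outcome and its analysis are both unsettled.

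On rank, a reader cannot tell whether a result on the Modified Ashworth scale would count towards the trial's main claim.

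On analysis, the scale is a set of ordered grades, one of which, 1+, has no numeric value. A t-test compares means, so someone must first assign a number to 1+. The spacing between grades, and therefore the mean difference and the p-value, follow from that choice. The grade is not a rare one in this trial, because it is written into the entry rule. The trial is open-label, and the investigators do the data monitoring and coding, so an unstated code leaves room for choice on an outcome that one section calls primary.

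**Working it through.** The plan gives no figure for this outcome to reproduce. The check asks whether the code given to 1+ can change a t-test result, and by how much.

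**Inputs**
- 20 patients per arm (Sample size).
- Unpaired t-test between arms (Data collection, management, and analysis methods).
- Assumption: the scale has six ordered grades, 0, 1, 1+, 2, 3, 4. The article does not list them.
- Hypothetical day-30 grades. They are not trial data, and they were picked from simulated trials because the codings disagree on them.

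| Arm | 0 | 1 | 1+ | 2 | 3 | 4 |
|---|---|---|---|---|---|---|
| A (control) | 2 | 7 | 7 | 4 | 0 | 0 |
| B (*Basti* added) | 2 | 15 | 3 | 0 | 0 | 0 |

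**Step 1: what one grade of improvement is worth.** Moving from 1+ to 1 is a change of −0.5 if 1+ = 1.5, −1 if grades are coded 0 to 5, and 0 if 1+ is merged with 1.

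**Step 2: t-test under each code.** With equal arms, t = (mean B − mean A) / (s × √(2/20)), where s is the pooled SD and √(2/20) = 0.316, on 38 degrees of freedom.

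For example, with 1+ = 1.5:
- mean A = (2×0 + 7×1 + 7×1.5 + 4×2)/20 = 25.5/20 = 1.275
- mean B = (2×0 + 15×1 + 3×1.5)/20 = 19.5/20 = 0.975
- difference −0.300, s = 0.486, t = −0.300/(0.486 × 0.316) = −1.95

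| Code for 1+ | Mean A | Mean B | Difference | s | t | p |
|---|---|---|---|---|---|---|
| 1.5 | 1.275 | 0.975 | −0.30 | 0.486 | −1.95 | 0.058 |
| 2 (grades coded 0–5) | 1.65 | 1.05 | −0.60 | 0.752 | −2.52 | 0.016 |
| 1 (merged with grade 1) | 1.10 | 0.90 | −0.20 | 0.447 | −1.41 | 0.165 |

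The grades are identical in all three rows, and the p-values fall on both sides of 0.05. The raw differences are in different units and should not be compared as effect sizes. The t and p columns carry the point.

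**Step 3: rank test.** A Mann-Whitney test on the six ordered grades uses only their order. It gives p = 0.020 under both codes that keep the order (1+ = 1.5, and 0–5). Merging 1+ with 1 discards part of the order, so the grades have to be kept distinct.

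**Step 4: how often it matters.** It does not always matter. If patients move only between 1, 1+ and 2, the 1.5 and 0–5 codes are linear versions of each other and give the same p. With A at 4/14/2 and B at 10/10/0 for grades 1/1+/2, p = 0.0228 under both. In 5,000 simulated trials under one assumed pair of grade distributions, these two codes disagreed at 0.05 in about 7%.

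**The case against.** The strongest case against has four parts.

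1. **The t-test may not be meant for this outcome.** The plan assigns it as "Unpaired ‘t’ test for objective variables" and does not say that the Ashworth grade is one of these. That is true, and applying it to the scale is an inference from the absence of any other test. If the inference is wrong, an outcome listed as primary has no stated test. Either way the text needs correcting.
2. **The coding may be fixed elsewhere.** A full protocol or SAP, neither of which is shown, could define it. That stands: nothing here shows that a code would be chosen after the data are seen. But the published method names t-tests alone, and a stated code would still leave a mean of ordinal grades.
3. **The effect is modest and not universal.** This also stands, as Step 4 shows. The example demonstrates what can happen and does not predict this trial's result.
4. **The entry rule is not itself an error.** A reader might infer that every patient starts at exactly 1+, so that baseline variance is zero and only two grades remain for improvement against three for worsening. The article does not support this. The entry sentence breaks off and can equally mean 1+ and above. It names no scale. No section ties the outcome to the ankle plantar flexors. Even a uniform entry grade would be a legitimate way to make the arms alike. A reader might also argue that tone could rise as movement returns and be counted as failure. That needs a meaning of stage that the article does not give, so it is not relied on.

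**Conclusion.** The point holds as a cheap improvement in method together with an internal contradiction. The contradiction in rank, primary under Variables to be measured and secondary in the Introduction, is plain from the text. The analysis defect is that an ordinal scale with a non-numeric grade sits under a plan that names only t-tests and gives no code. For the same hypothetical grades, p ranges from 0.016 to 0.165 across three codes, while a rank test on the ordered grades gives 0.020.

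This rests on three assumptions: that the scale has the six grades listed above, that the t-test is meant to cover this outcome, and, for the link to the entry rule only, that 1+ there is a Modified Ashworth grade. The need for a code stands under either reading of the entry sentence, because 1+ can occur at entry or follow-up in both. The missing improvement criterion for this scale fits the same picture but is a separate, minor gap.

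**What to change.** - **Variables to be measured:** move the Modified Ashworth scale out of the primary list so that it agrees with the Introduction's secondary goal, align the Abstract, and name the muscle group and side scored.
- **Data collection, management, and analysis methods:** for this outcome, replace the t-test with a rank (ordinal) comparison between arms on the ordered grades 0, 1, 1+, 2, 3, 4, kept distinct. If entry allows more than one grade, compare the change from each patient's own baseline grade. Report the number of patients at each grade by arm and visit.
- **Eligibility criteria:** complete the unfinished sentence by stating the scale and whether 1+ is an exact grade or a minimum, and reconcile it with the outcome definition. Which of these is intended is for the investigators to state.

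The cost is wording only. The patients, visits and measurements stay the same. The small downside is that the result is a shift in grades and not a mean difference.

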### Interventions

For group A, standard control modern treatment (Anti-thrombotic treatment, e.g. Tab. Ecosprin 75/150 mg OD and Tab. Notropril 800 mg TDS) will be given along with physiotherapy. The physiotherapy sitting for motor relearning program and functional stimulation will be given for 55 mins per sitting, five days weekly for one month.

For group B, standard control modern treatment will be given along with Ayurveda Panchakarma and physiotherapy. In this case, gentle massage with
*Dashmoola Taila* +
*Nadi Sweda* with
*Dashmoola Kwatha* + medicated enema (alternate regime of
*Dashamoola Niruha Basti* with
*Anuvasana Basti* with
*Dashmoola Taila* will be prescribed for the treatment. The alternative regime of medicated enema i.e.,
*Anuvasana Basti* (oil enema) and
*Dashamoola Niruha Basti* (decoction enema) will be given on odd and even days respectively for one month, and physiotherapy for five days weekly for one month.

The study’s methodology is mentioned in
Table 1 and the flowchart of the study design or methodology is given in
Figure 1.

**Table 1. T1:** Methodology of the study.

Group	Sample size	Intervention	Type of Treatment	Duration of treatment	Total duration	Follow-up
**A**	20	Standard Control	Modern + Physiotherapy (MRP+FES)	For Physiotherapy sitting (55 mins/sitting)	Physiotherapy (Five days weekly for one month)	on 60 ^th^ & 90 ^th^ Day
**B**	20	Standard Control + *Panchakarma*	Modern + Physiotherapy (MRP+FES) Gentle massage with *Dashmoola Taila* + *Nadi Sweda* with *Dashmoola Kwatha* + Medicated Enema (Alternate regime of *Dashamoola Niruha Basti* with *Anuvasana Basti* with *Dashmoola Taila*	• Same as group A+ *Dashmoola Basti* Details of *Dashmoola Basti* Are as follows: • Local *Snehana*-10 mins • Local *Swedana*-10 mins or till attainment of *Samyak Swinna Lakshana*, whichever is earlier.	• Panchakarma for complete one month (Day 1 ^st^ – Day 30 ^th^) • Physiotherapy for Five days weekly for one month	on 60 ^th^ & 90 ^th^ Day

* FES – Function Electrical Stimulation, MRP – Motor Relearning Programme.

